**Table 1 Tab1:**
[figure not shown]
The schedule of enrolment, interventions, and assessments of this study protocol

Outcomes assessment will be administered to participants at baseline, immediately after the intervention, and 3 months after the end of the intervention. The baseline assessment will take place within 1 week before the start of the intervention, and the postintervention assessment will be administered within 1 week after the end of the intervention. Table 1 presents the timing of all study procedures.

### Intervention

The PRI and DRI groups will receive an equal amount of treatment time, comprising 1.5 h per day, 3 days per week, for 6 weeks. All other routine interventions, such as physical therapy or medication, will continue as usual throughout the study period, except for the administration of botulinum toxin.

### PRI group

The PRI protocol provides RT for 45 min and IOT for 45 min. The PRI group will start from the Bi-Manu-Track proximal mode (i.e., forearm RT) and then the distal mode (i.e., wrist RT). In every session of RT, the patient will practice bilateral passive range of motion exercise, in which the unaffected side assists the affected UE, and bilateral active range of motion exercise. RT will be followed by IOT.

The IOT will be delivered according to the participant’s motor ability, namely, the Arm BASIS training (focusing on basic motor control) for severe arm paresis and Arm Ability training (focusing on complex motor control) for mild arm paresis [12]. Participants who score less than 35 in the baseline UE-FMA subscale and cannot achieve a precision grip will be assigned to the Arm BASIS training, and the other participants will receive the Arm Ability training [12].

### DRI group

The DRI protocol is similar to the PRI protocol but starts from the Bi-Manu-Track distal mode (i.e., wrist RT) and then the proximal mode (i.e., forearm RT). The participants will receive 45 min of RT, followed by 45 min of IOT, which is the same as in the PRI group. RT will include passive-passive, active-passive, and active-active range of motion exercise.

### Primary outcome measurements

The **UE-FMA** is used to assess motor impairment of body function, including ranges of motion of the UE joints, and grasping, coordination, and speed of UE movement. The UE-FMA is scored on a 3-point ordinal scale (0 = cannot perform, 1 = perform partially, 2 = perform fully), with a total score between 0 and 55. A higher UE-FMA score means better motor performance and less impairment.

The **Medical Research Council Scale (MRC)** measures muscle power of the affected UE joints. The MRC is scored on a 6-point ordinal scale (0 = plegic, 5 = resisted to maximal strength, full power compared with the unaffected side).

The **Revised Nottingham Sensory Assessment (rNSA)** is used to assess sensory impairment, including pressure, temperature, light touch, kinesthetic sense on the shoulder, elbow, wrist, and hand, and stereognosis. The rNSA is scored on a 3-point ordinal scale (0 = absent, 1 = impaired, 2 = normal), with a total score of 48. The rNSA has acceptable inter-rater reliability.

The **Wolf Motor Function Test (WMFT)** assesses functional motor ability of the UE with 15 functional tasks. The patient is requested to perform tasks as quickly as possible and use the affected side in task performance. Average time (WMFT-Time) and functional ability score (WFMT-FAS) are reported.

### Secondary outcome measurements

The **10-Meter Walk Test (10MWT)** is used to assess walking speed.

The **MyotonPro** is a handheld device that can measure muscle mechanical properties of patients positioned supine.

The **Actigraphy** is a device that is worn on the wrist and may record activity levels of the patient’s UE.

The **Functional Independence Measure (FIM)** is an 18-item measurement tool that assesses a patient’s level of physical, psychological, and social functioning, and disability.

The **Motor Activity Log (MAL)** is a semistructured interview of 30 items and is used to assess the amount of use of the affected UE and the quality of the movement during functional daily activities.

The **ABILHAND Questionnaire** is an inventory of 23 manual activities on which the patient provides his or her self-perceived performing difficulty on a 3-level scale (impossible, difficult, easy) [16].

The **Nottingham Extended Activities of Daily Living Scale (NEADL scale)** is used to measure a patient’s independence in instrumental activities of daily living in the past few weeks across four domains: mobility, kitchen, domestic, and leisure activities.

The **Stoke Impact Scale (SIS) 3.0** is a 59-item questionnaire that measures perceived disability and health-related quality of life after stroke in eight domains: strength, hand function, activities of daily living/instrumental activities of daily living, mobility, communication, emotion, memory/thinking, and participation/role function. A Rasch analysis of the psychometric property of the SIS 3.0 showed good reliability and validity [17].

The **Goal Attainment Scale (GAS)** is an individualized outcome measure for goal setting in an intervention and goal scaling to estimate the extent to which the patient’s goals are met.

The **Stroke Self-Efficacy Questionnaire (SSEQ)** is a 13-item questionnaire that evaluates self-efficacy in functioning after stroke.

### Statistical analyses

The Student *t* test and *χ*^2^ will be used to analyze differences in baseline characteristics and outcome measures between the two groups. Two-way repeated-measures of analysis of variance will be used to determine the intervention effects. The within-subject factor is time (i.e., pretest, posttest, and follow-up assessment), and the between-subject factor is group (i.e., PRI and DRI). A post hoc Tukey test will be used when a group × time interaction or a main effect is observed. An *α* level of .05 is set for all statistical comparisons. Partial eta squared (*η*^2^) will also be estimated to determine the group difference for each outcome measure. Predictors of PRI and DRI outcomes will be estimated with the chi-square automatic interaction detector (CHAID) method. Data analyses will be performed using SPSS Statistics 18.0 software (IBM Corp, Armonk, NY, USA).

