This study is therefore designed to extend the previous study [12] by examining the effect of proximal (i.e., forearm first and wrist second) priority robotic priming and impairment-oriented training (PRI) and distal (i.e., wrist first and forearm second) priority robotic priming and impairment-oriented training (DRI) with a larger sample size (i.e., *n* = 20 in each group). We hypothesize that the PRI and DRI groups will both improve significantly on normalized muscle tone, sensorimotor impairment, upper limb function, self-efficacy, and quality of life from preintervention to postintervention and that the improvement will be maintained at the follow-up assessment. In addition, this study will compare the relative effects between PRI and DRI. We hypothesize that the PRI group will achieve better proximal UE motor ability and that the DRI group will achieve better distal UE motor ability.

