### Design and procedure

The study will use a single-blind randomized pretest and posttest design. Potential participants will be identified by the therapists or research assistants, and the study procedures, risks, and benefits will be explained. All participants will sign the informed consent before enrolling in this study and be allocated to the PRI or DRI groups based on a computer-generated random-sequence table (Table 1). The second author of this study ([name]) will generate the allocation sequence, enroll participants, and assign participants to interventions. Allocation concealment is ensured, as the computer-generated random codes are not released. The study will recruit 40 patients with stroke from hospital settings. Initial and outcome assessments will be administered by a well-trained and certified occupational therapist who is blinded to the group assignment, study hypotheses, and intervention of the patients. Trial participants, care providers, outcome assessors, and data analysts will be blinded after assignment to interventions. Unblinding is permissible when knowledge of the actual treatment is absolutely essential for further management of the patient.

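### Unless missing values are imputed first, the stated repeated-measures ANOVA drops every participant who lacks any one of the three assessments, including those with observed pretest and posttest values

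*Protocol article*

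**What the plan says.** The protocol article, under Statistical analyses, names one method for the intervention effects: "Two-way repeated-measures of analysis of variance will be used to determine the intervention effects". Its structure is given next: "The within-subject factor is time (i.e., pretest, posttest, and follow-up assessment), and the between-subject factor is group (i.e., PRI and DRI"). A Tukey test follows if an effect is found. On significance, an alpha "level of .05 is set for all statistical comparisons". Partial eta squared "will also be estimated to determine the group difference for each outcome measure". On software: "Data analyses will be performed using SPSS Statistics 18.0 software".

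On size, Design and procedure says: "The study will recruit 40 patients with stroke from hospital settings". The Background presents 20 per group as an advance over the pilot, "with a larger sample size", and the Discussion concedes that 20 per group is small. The last assessment is 3 months after treatment ends. The article gives no expected loss, analysis set or missing-data rule. It does not say that incomplete participants will be excluded.

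**The concern.** A sum-of-squares repeated-measures ANOVA works on complete rows. With time at three levels, a row is complete only if pretest, posttest and follow-up are all present. Partial eta squared belongs to that procedure rather than to a likelihood-based mixed model, and the repeated-measures GLM in SPSS deletes incomplete rows listwise. So a participant with pretest and posttest who misses only the late visit leaves the whole ANOVA, including the pre-to-post part for which both values exist.

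The article's hypotheses are improvement from before to after treatment, maintenance at follow-up, and differences between PRI and DRI. All three rest on this one analysis. Two things are at stake: precision in a trial of 40, and, if the people lost are those who gained least, the size of the reported improvement.

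**Working it through.** **Inputs from the article.** 20 per arm, 40 in total; three assessments; alpha .05 (taken as two-sided where a t test is used). No power, effect size, SD or loss rate is given, so there is no stated power figure to reproduce. The only check on the sample size is 2 × 20 = 40.

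**Assumed inputs.** Loss rates, correlations, the true difference and the reasons for missing visits are all assumptions.

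**1. Number analysed.** If a share d of participants miss at least one assessment, completers per arm are 20(1 − d):

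| d | completers per arm | total |
|---|---|---|
| 5% | 19 | 38 |
| 10% | 18 | 36 |
| 15% | 17 | 34 |
| 20% | 16 | 32 |
| 25% | 15 | 30 |

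The chance that all 40 are complete is (1 − d)^40: 0.95^40 = 12.9% and 0.90^40 = 1.5%. Even modest loss makes some shortfall likely.

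**2. Power.** Simulation with 20 per arm, unit SD, correlations .75 (pre-post), .85 (post-follow-up) and .70 (pre-follow-up), a true PRI-DRI difference of 0.6 SD at both later visits, and follow-up missing at random:

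| Missing follow-up | Group × time ANOVA, complete cases | Baseline-adjusted posttest ANCOVA, all posttests | Same ANCOVA, three-visit completers only |
|---|---|---|---|
| 0% | 76% | 78% | 78% |
| 10% | 71% | 79% | 73% |
| 20% | 66-67% | 79% | 69% |

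The first column shows the cost: about 5 points at 10% loss and about 10 at 20%. The second column is a different test and is already slightly ahead with no loss, so the gap between columns one and two is not all due to missing data. The third column is the like-for-like check: the same ANCOVA loses about 6 and 10 points when observed posttests are discarded.

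**3. Bias.** A second simulation used correlations .7 (pre-post), .6 (pre-follow-up) and .7 (post-follow-up), a true pre-to-post gain of 0.50 SD in both arms, and a follow-up more likely to be missed by those with a small observed gain:

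| Who is lost | Average number analysed | Completer pre-to-post gain (true 0.50) | Completer PRI-DRI difference (true 0) |
|---|---|---|---|
| Poor responders, both arms | about 35 | 0.60 | 0.00 |
| Poor responders, both arms | about 30 | 0.66 | 0.00 |
| Poor responders, one arm only; random loss in the other | about 35 | 0.55 | 0.09 |
| Poor responders, one arm only; random loss in the other | about 31 | 0.58 | 0.16 |

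Using all observed pretest and posttest values, the gain was 0.50 and the PRI-DRI difference 0.00 in every row. Under loss completely at random, only precision suffers.

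**The case against.** The strongest reply is that this is a missing-data omission presented as a method error. The article neither states nor rules out imputation before the ANOVA, and a full protocol or SAP that is not shown may settle it. That stands as a condition: the loss occurs only if someone misses a visit and nothing is imputed. It does not remove the point, because the article itself names the procedure, the effect measure and the software, and together they lead by default to complete rows.

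Some stronger readings are tempting but unsupported:

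- *That 20 per arm will not be analysed.* The article gives group and recruitment sizes, not an analysed number, and no power calculation is contradicted. Its claim of a larger sample is relative to the pilot's group of 10, and 15 per arm is still larger.
- *That incomplete participants leave every comparison.* The t tests, chi-square tests and CHAID analysis in the same section do not inherently need three visits.
- *That the PRI-DRI result will be biased.* Both arms receive 45 minutes of robot training and 45 minutes of impairment-oriented training with only the robot order reversed, and participants are said to be blinded. Nothing suggests that loss would differ by arm, and without such a difference the simulated contrast was unbiased.
- *That a better model would restore power to 78-79%.* That figure belongs to a posttest ANCOVA which, when only follow-up is missed, loses no data by construction.

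**Conclusion.** The point holds in conditional form. As stated, and without prior imputation, the ANOVA discards observed pre-to-post data from anyone who lacks one of the three assessments. Under the assumed 0.6 SD difference and correlations, 10-20% missing follow-up costs roughly 5 to 10 points of group-by-time power. If poor responders are the ones lost, a true gain of 0.50 SD could be read as 0.60-0.66 SD. A spurious PRI-DRI difference needs loss that differs by arm, for which the article gives no reason. The mechanism follows from the stated method; every size depends on assumed inputs. The change is worth making because it is cheap and keeps data already collected.

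**What to change.** In Statistical analyses, replace the repeated-measures ANOVA with a likelihood-based linear mixed model:

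- all randomised participants, in the arm assigned;
- all available pretest, posttest and follow-up values as outcomes;
- time (three levels), group and group × time, with unstructured covariance;
- a small-sample degrees-of-freedom correction such as Kenward-Roger or Satterthwaite.

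Report, with 95% confidence intervals, the within-arm change from pretest to posttest and to follow-up, and the PRI-DRI difference in change at each later visit. The PRI-DRI contrasts may instead come from a model of posttest and follow-up adjusted for pretest. The pretest must enter one way or the other: a model of the later visits alone cannot estimate the hypothesised improvement, and has only about 45% posttest power in the scenario above.

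Revise the Tukey and partial eta squared wording to match. Keep the complete-case ANOVA as a sensitivity analysis, and report the number analysed at each visit.

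The cost is a few sentences of wording, slightly more analysis work and a missing-at-random assumption to state. No extra patients, visits or data are needed.

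### The group × time ANOVA counts pretest as an outcome visit and does not say which term tests PRI against DRI; a group main effect would be diluted by a third, and a baseline-adjusted contrast is generally more efficient than the interaction

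*Protocol article*

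**What the plan says.** All of the analysis text is in the Statistical analyses section of the protocol article.

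- Purpose of the model: "Two-way repeated-measures of analysis of variance will be used to determine the intervention effects".
- Its factors: "The within-subject factor is time (i.e., pretest, posttest, and follow-up assessment), and the between-subject factor is group (i.e., PRI and DRI").
- What is acted on: "A post hoc Tukey test will be used when a group × time interaction or a main effect is observed". The text does not say whether the main effect is that of group, of time, or either.
- Effect size: partial eta squared "will also be estimated to determine the group difference for each outcome measure". No ANOVA term is named.
- Significance level: an α "level of .05 is set for all statistical comparisons".

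Pretest scores otherwise appear only in t tests and χ² tests comparing the arms at baseline. No covariate or change score is stated. The Design and procedure section places pretest before any treatment: "The baseline assessment will take place within 1 week before the start of the intervention". It also fixes the size of the trial: "The study will recruit 40 patients with stroke from hospital settings", which the Background and Discussion give as 20 per group.

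The Background ends with two kinds of hypothesis. One is within-group: both arms improve and keep the gain at follow-up. The other is between-group: PRI does better proximally and DRI distally.

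**The concern.** In a model with two groups and three visits, the group main effect is the PRI-DRI difference averaged over all three visits. One of these precedes treatment and can hold no treatment effect, only the chance difference in starting scores. A group main effect is therefore a diluted estimate of the treatment difference, mixed with baseline imbalance. The plan's wording allows this term to trigger follow-on comparisons, and it is a natural reading of an effect size for the group difference.

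The other route, the group × time interaction, is a sound test of differential change. It has 2 degrees of freedom, and it handles pretest as a noisy outcome rather than as a known starting value. With 20 patients per arm, which the Discussion itself calls small, efficiency matters. So does knowing in advance which number answers the PRI-DRI question.

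**Working it through.** **Inputs from the protocol.** 40 patients, 20 per arm; three visits, the first before treatment; α = .05.

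**Assumptions, because the protocol gives no SD, correlation, effect size or power.** Two-sided tests; SD of 1 at every visit; the same correlation r between any two visits (compound symmetry), r = .6, .7 or .8; true PRI-DRI difference d = 0.6 SD at posttest. There is no stated power figure to reproduce. Write v = 2/20 = 0.1.

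**1. Dilution of the group main effect.** It estimates (0 + d + d)/3 = 2d/3, so 0.6 SD becomes 0.4 SD. Against the mean of the two later visits the ratio is 2/3 whatever the profile. For example, an effect that has gone by follow-up gives d/3 against d/2.

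**2. Carry-over of a chance pretest difference b.** With no treatment effect, the expected difference given b is b at pretest and rb at each later visit. The group main effect is then expected to be b(1 + 2r)/3. For b = 0.5 SD:
- r = .6: 0.5 × 2.2/3 = 0.37 SD
- r = .7: 0.5 × 2.4/3 = 0.40 SD
- r = .8: 0.5 × 2.6/3 = 0.43 SD

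A baseline difference of 0.5 SD would not be flagged at 20 per arm, where the critical observed difference is 0.64 SD. A pretest-adjusted estimate has expectation 0.

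**3. Type I error.** Averaged over randomisations, the group main effect keeps its level (4.9% in 20,000 simulated null trials at r = .8). Given an observed pretest difference of two standard errors (2 × √0.1 = 0.63 SD) and no treatment effect, the chance of a significant group main effect is about 29% at r = .5 and 39% at r = .8 (normal approximation).

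**4. Power, from the noncentral F distribution.**
- Group main effect: noncentrality (2d/3)² / [v(1 + 2r)/3], df 1, 38. At r = .7: 0.16/0.08 = 2.0.
- Interaction: Σ(δ − mean δ)² / [v(1 − r)], df 2, 76. For δ = (0, 0.6, 0.6) and r = .7: 0.24/0.03 = 8.0.
- ANCOVA at posttest alone: d² / [v(1 − r²)], df 1, 37. At r = .7: 0.36/0.051 = 7.06.
- ANCOVA on the mean of posttest and follow-up: (mean effect)² / [v((1 + r)/2 − r²)], df 1, 37. At r = .7 with full persistence: 0.36/0.036 = 10.0.

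| Test | Effect at follow-up | r = .6 | r = .7 | r = .8 |
|---|---|---|---|---|
| Group main effect | 0.6 SD | .30 | .28 | .26 |
| Interaction | 0.6 SD | .57 | .70 | .87 |
| Interaction | 0.3 SD | .44 | .57 | .75 |
| Interaction | 0 | .57 | .70 | .87 |
| ANCOVA, posttest alone | any | .64 | .73 | .87 |
| ANCOVA, mean of both | 0.6 SD | .80 | .87 | .95 |
| ANCOVA, mean of both | 0.3 SD | .55 | .64 | .78 |
| ANCOVA, mean of both | 0 | .29 | .34 | .44 |

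The interaction has the same power when the effect persists fully and when it has gone, because Σ(δ − mean δ)² is 0.24 for both profiles.

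**The case against.** The strongest reply is that the protocol never says a group main effect is evidence for one arm over the other. The sentence sets when a Tukey test is run. Group has two levels, so a Tukey test on it adds nothing to the F test; time has three, where pairwise follow-up makes sense. A time main effect is also what the within-group hypothesis needs, and that hypothesis requires pretest as a level of time. This stands. A reader might infer that the plan commits to the group main effect as its treatment comparison, but the text leaves this open. What remains is that the wording does not exclude it, and that the effect size for the group difference has no term attached.

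Second, the interaction is already planned, is valid and is not diluted by pretest. This also stands, and the choice between it and ANCOVA is one of efficiency.

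Third, a reader might infer from the highest ANCOVA figures (.80/.87/.95) that the plan wastes a great deal of power. Those figures need the effect to persist in full at follow-up, which the protocol does not establish. Against ANCOVA at posttest alone, the interaction loses 7, 3 and 0 percentage points. If the effect has gone by follow-up, the interaction beats ANCOVA on the mean. Durability is also among the trial's aims, so a difference between posttest and follow-up is not irrelevant.

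Fourth, a reader might infer an inflated false-positive rate. There is none overall. The problem is how to interpret a result once a baseline difference has been observed.

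Finally, a condensed article may leave contrasts and covariates to a fuller plan. That would excuse silence, but here the model, its levels and its triggers are stated, and the point concerns what is stated.

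**Conclusion.** The point holds as one of specification and efficiency; it does not make the planned analysis invalid. As written, the plan permits a group main effect averaged over pretest to be read as PRI versus DRI. Under that reading a true difference shrinks by a third, and 0.37 to 0.43 SD of a 0.5 SD chance pretest difference would pass for treatment effect. The interaction has neither the dilution nor an inflated error rate. It is generally somewhat less powerful than a pretest-adjusted contrast: by 0 to 7 points against ANCOVA at posttest, and by more against the mean contrast if the effect lasts (8 to 23 points with full persistence, 3 to 11 if it halves). The mean contrast loses that advantage if the effect fades completely.

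The 2/3 ratio depends only on pretest carrying no treatment effect. The carry-over and power figures rest on the assumed equal SDs, compound symmetry and correlations of .6 to .8; the powers rest also on the assumed 0.6 SD difference.

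**What to change.** For the PRI-DRI comparison of each outcome:

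- Model posttest and follow-up, with that outcome's own pretest score as covariate plus group, visit and group × visit.
- Name in advance the adjusted contrast at posttest as the main comparison, and report the adjusted contrast at follow-up separately. This choice does not depend on how long the effect lasts.
- Tie the effect size to that contrast.
- State that a group main effect averaged over pretest is not evidence of a PRI-DRI difference.

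Keep the three-level time effect (pretest, posttest, follow-up) for the hypothesis of within-group improvement and maintenance, and say that the post hoc main-effect comparisons refer to time.

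The pretest scores are already collected, so no further patients or visits are needed. The cost is one degree of freedom per outcome and a second model to describe and report.

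### The PRI–DRI model has only group and time and omits the IOT programme that baseline severity assigns for half of every session: a loss of precision, not a bias

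*Protocol article*

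**What the plan says.** **Model.** Under Statistical analyses, the plan for efficacy is a two-factor repeated-measures ANOVA. Three visits, the pretest among them, make up the within-subject part. For the comparison of the arms, "the between-subject factor is group (i.e., PRI and DRI". The same section plans baseline t and χ² tests and a CHAID analysis of predictors. It links neither to the between-group comparison.

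**Programme.** Under PRI group, the rule for the first programme reads: "score less than 35 in the baseline UE-FMA subscale and cannot achieve a precision grip will be assigned to the Arm BASIS training". Everyone else has Arm Ability training. IOT takes 45 minutes after 45 minutes of robot training. The DRI group section gives the same split and the same IOT, so the rule applies in both arms. The inclusion range for UE-FMA, 18 to 56, lies on both sides of the cut at 35, so both programmes can be expected to occur.

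**Allocation and size.** Under Design and procedure, participants will "be allocated to the PRI or DRI groups based on a computer-generated random-sequence table". The type of sequence is not described further. The Background plans 20 per group.

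**The concern.** The PRI–DRI contrast carries the sequence hypothesis. Both arms receive the same components for the same time and differ only in the order of the two robot modes, so the effect to be detected may be modest. The programme filling the other half of each session is known before treatment and depends on severity. The article itself describes the two programmes as developed for different severity levels.

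If Arm BASIS and Arm Ability participants improve by different amounts, a model without programme treats that difference as noise. It also has no means of correcting an uneven programme mix between the arms. The article calls its own sample small, so an avoidable loss of precision matters.

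**Working it through.** The article states no power, effect size or SD, so there is no figure to reproduce. The question is how much the omitted factor could matter.

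**Inputs.** From the article: 40 participants, 20 per group; IOT 45/90 = 50% of each session; α = 0.05 (two-sided assumed). Not in the article, hence assumed: the Arm BASIS share p, 0.3 to 0.5 (12 to 20 of 40), and the difference D in mean gain between programmes, 0.5 to 1.0 within-programme SD.

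**1. What the stated model already handles.** Because the pretest is a level of time, the group × time test compares changes, and an additive baseline severity difference cancels. What remains is a difference in gain by programme. The group main effect, which the plan also follows up, does take in a difference in level.

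**2. Residual variance.** Without programme, the variance of change is 1 + p(1−p)D² in within-programme units. The share removed by fitting programme is p(1−p)D² / [1 + p(1−p)D²].

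| p | D | p(1−p)D² | variance removed | standard error smaller by |
|---|---|---|---|---|
| 0.3 | 0.5 | 0.0525 | 5.0% | 2.5% |
| 0.3 | 1.0 | 0.21 | 17.4% | 9.1% |
| 0.5 | 0.5 | 0.0625 | 5.9% | 3.0% |
| 0.5 | 1.0 | 0.25 | 20.0% | 10.6% |

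**3. Cost of the term.** If allocation is not stratified, group and programme are correlated by chance, with expected squared correlation 1/(40−1) = 2.6%. This raises the variance of the group estimate by about 39/38 = 1.026, or about 1.3% in standard error. Net variance ratios are 1.026/1.0525 = 0.975 at the low end (standard error 1.3% smaller) and 1.026/1.25 = 0.821 at the high end (9.4% smaller).

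**4. Chance imbalance, if allocation is not stratified.** With arms fixed at 20/20, the number of Arm BASIS participants in one arm is hypergeometric. For 12, 16 and 20 such participants in total:
- P(arms differ by 4 or more) = 0.301, 0.333, 0.343
- P(arms differ by 6 or more) = 0.082, 0.105, 0.113

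A gap of 4 is 4/20 = 20 percentage points and shifts the contrast by 0.20 × D = 0.10 to 0.20 SD. The standard error with programme fitted and balanced is √(2/20) = 0.316 SD, so the shift is about one third to two thirds of a standard error.

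**5. Simulation.** Change scores were analysed with and without a programme term (20,000 replicates per setting, 20/20, unstratified). Power is at 0.886 SD, the effect that 20 per arm detects with 80% power by the normal approximation.

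| p, D | type I error overall, without / with term | type I error given a gap of 6 or more, without / with | power, without / with |
|---|---|---|---|
| 0.4, 0.5 | 5.2% / 5.1% | 7.1% / 4.9% | 75.6% / 77.1% |
| 0.4, 0.8 | 4.9% / 4.8% | 9.4% / 4.3% | 71.7% / 76.7% |
| 0.5, 1.0 | 5.3% / 5.1% | 13.2% / 4.2% | 68.2% / 76.5% |

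Overall error is near 5% either way. The term improves power and restores the error rate in trials that happen to be badly imbalanced.

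**6. Form of the term.** In a repeated-measures ANOVA, a programme main effect affects only the average over visits. It drops out of the within-subject contrasts and leaves the group × time test unchanged. Programme × time is needed as well.

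**The case against.** The strongest reply is that an unadjusted group × time ANOVA in a randomised trial is valid. Both arms use the same programme rule, overall type I error holds, and a shift of 0.10–0.20 SD is ordinary chance variation already covered by a standard error of about 0.32 SD. All of this stands, and it limits the point to precision and to behaviour under an actual imbalance.

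The size is also assumed. The article gives no gain by programme. IOT is tailored to severity, so gains could be similar and the benefit would then be negligible. This stands too, and is why ranges are given.

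Programme is largely determined by baseline UE-FMA, so in a model that already adjusts for baseline UE-FMA it may add little. The variance figures above are for programme without baseline adjustment and should not be added to what an ANCOVA gains.

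A reader might go further and infer that the sequence is simple and unrestricted, so that 20 per group is unlikely and the programme mix unprotected by design. The article does not support that. It mentions a computer-generated table without saying whether it has blocks or strata, the plan of 20 per group hints at some restriction, and a condensed article commonly leaves such detail to the full protocol. The omission from the model does not depend on this, since an allocation stratified by programme would also call for the term.

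**Conclusion.** The point holds as a matter of precision. The article fixes a model with time and group only, while a baseline rule assigns two different programmes that occupy half of every session, and neither the baseline tests nor CHAID brings that factor into the PRI–DRI comparison.

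The gain from fitting it is about 5–20% of residual variance under the assumed ranges, reduced by roughly 1% in standard error for the term itself. The imbalance probabilities apply only if allocation is not stratified by programme. A reader might take the omission as biasing the contrast; it does not, because the rule is common to both arms and group × time already removes additive baseline differences. This is an inexpensive improvement to a small trial, not a defect that invalidates its analysis.

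**What to change.** In Statistical analyses, prespecify IOT programme (Arm BASIS / Arm Ability, as determined at baseline) in the PRI–DRI comparison, by one of two routes:

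- keep the repeated-measures ANOVA and add both programme and programme × time; or
- analyse post-test and follow-up scores by ANCOVA on group, baseline value and programme.

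The second changes the type of model, because the pretest moves from an outcome level to a covariate. Fix the choice before any results by group are seen.

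No new data are needed, since UE-FMA and grip are already assessed to assign the programme. The ANOVA route costs 1 between-subject degree of freedom plus 2 for programme × time. The gain is small if the programmes produce similar improvement.
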